#### Vascular function and structure

A random sub-sample of patients will undertake the vascular assessments. All vascular assessments will be performed in the supine position and by an experienced investigator blinded to the group allocation.

Carotid intima-media thickness will be assessed according to current guidelines [51]. Patients will remain with the head rotated to the left and a linear transducer (7–10 MHz) attached to a high-resolution ultrasound machine (GE Logiq E, GE Medical, Milwaukee, WI, USA) will be positioned perpendicularly to the right common carotid artery (i.e., longitudinal plane), 1–2 cm below the bifurcation. Ultrasound parameters will be modified to optimize the appearance of the intima border along the vessel. Measurements will be performed in three distinct angles and will be recorded for 30 s. The analysis of carotid intima-media thickness will be performed using edge detection and wall tracking software (Cardiovascular Suite, Quipu®, Pisa, Italy).

Flow-mediated dilation of the brachial and superficial femoral arteries will be assessed according to current guidelines [52]. For brachial flow-mediated dilation, patients will be positioned with their right arm extended at an angle of ~ 80° from the torso and immobilized with foam supports. A manual pneumatic cuff will be positioned at the forearm to provide the ischemic stimulus. A linear transducer (7–10 MHz) attached to a high-resolution ultrasound machine (GE Logiq E, GE Medical, Milwaukee, WI, USA) will be used to assess brachial artery diameter at the distal third of the upper right arm. For superficial femoral artery flow-mediated dilation analysis, patients will be positioned with their right thigh externally rotated, the cuff will be positioned 1–2 cm above the knee, and the ultrasound transducer will be placed on the distal thigh.

When a satisfactory image is acquired, the probe will be kept stable and the ultrasound parameters will be set to optimize the B-mode image of the lumen-arterial wall interface. Continuous Doppler blood flow velocity will also be analyzed using an insonation angle ≤ 60° and the sample volume will be placed in the middle of the artery. Initially, a 1-min baseline diameter and blood flow velocity recordings will be acquired and then the forearm cuff will be inflated (~ 200 mmHg) for 5 min. Recordings will be resumed 30 s before cuff deflation and continued for 3 min thereafter (5 min for the superficial femoral artery).

Offline analyses of diameters, blood flow, and shear rate will be performed using edge detection and wall tracking software (Cardiovascular Suite, Quipu®, Pisa, Italy). Flow-mediated dilation will be calculated as the percentage rise (peak − baseline) in brachial/superficial femoral diameter obtained after cuff release in relation to the preceding baseline diameter. Time to peak dilation, and baseline anterograde and retrograde shear rate will be calculated as described elsewhere [52].

#### Health-related quality of life

Health-related quality of life will be assessed by the SF-36 questionnaire [53], in which scales (physical function, role-physical, bodily pain, general health, vitality, social function, role-emotional) range from 0 to 100. Higher scores indicate better quality of life.

#### Blood sample processing and analysis

Blood samples (40 ml) will be collected after a 12-h overnight fast, for measuring the following: glucose, insulin, c-peptide, glycosylated hemoglobin (Hb_A1C_), lipid profile (i.e., high-density lipoprotein (HDL) cholesterol, low-density lipoprotein (LDL) cholesterol, very low-density lipoprotein (VLDL) cholesterol, total cholesterol, and triglycerides), C-reactive protein, erythrocyte sedimentation rate, and cytokines (i.e., IFN-γ, IL-1, IL-1ra, IL-4, IL-6, IL-10, monocyte chemoattractant protein 1 (MCP-1), and TNF-α). Blood samples will be collected in vacutainer tubes and subsequently analyzed at the Clinical Hospital Central Laboratory (School of Medicine, University of Sao Paulo). An aliquot will be centrifuged and stored at − 80 °C for analysis of cytokines and other molecular analyses. A summary of these analyses is provided in Fig. 5.

**Fig. 5 Fig5:**
[figure not shown]
Summary of the blood and muscle analyses. ACACA, acetyl-coenzyme A carboxylase α; Akt, protein kinase B; AS160, Akt substrate of 160 kDa; AMPK, phosphorylated 5′ adenosine monophosphate-activated protein kinase; CRP, C-reactive protein; ESR, erythrocyte sedimentation rate; GLUT4, glucose transporter type 4; HbA1C, glycosylated hemoglobin; Lipid profile (triglycerides, total cholesterol, HDL, LDL, and VLDL); LPL, lipoprotein lipase; OXPHOS, oxidative phosphorylation complexes; PDK4, pyruvate dehydrogenase kinase 4

Glucose will be assessed using a colorimetric enzymatic assay (Bioclin, Belo Horizonte, Brazil). Insulin and peptide-C will be assessed using a radioimmunoassay technique (Diagnostic Products Corporation, Sao Paulo, Brazil). Total cholesterol, HDL, LDL, VLDL, and triglycerides will be assessed using enzymatic colorimetric assays (CELM, Sao Paulo, Brazil). C-reactive protein will be determined by immunoturbidimetry. Erythrocyte sedimentation rate will be assessed using an automated analyzer. Cytokines will be analyzed through a multiplex human panel (Billerica, MA, EMD Millipore, Milliplex®).

#### Oral glucose tolerance test

A 2-h oral glucose tolerance test will be performed at PRE and POST. Blood samples will be collected after a 12-h overnight fast, and at 30, 60, 90, and 120 min after ingestion of 75 g of glucose. Area under the curve (AUC) for glucose, insulin, and C-peptide, and Matsuda index, homeostatic model assessment-insulin resistance (HOMA-IR) and HOMA-B cell function (HOMA-B) will be calculated as surrogates of insulin resistance.

#### Lipidomics (non-targeted)

PRE and POST intervention serum samples (10 μL) will be collected from a random sub-sample of 20 patients (Fig. 5). Samples will be extracted in a single-phase extraction with 200 μL of CHCl3:MeOH (2:1) and 10 μL of an internal standard mix containing between 50 and 1000 pmol each of 23 non-physiological and stable isotope-labeled lipid standards. Sample analysis will be performed by electrospray ionization tandem mass spectrometry with the use of an Agilent 1200 liquid chromatography system combined with an Applied Biosystems API 4000 Q-TRAP mass spectrometer with a turbo-ion spray source (350 °C) and Analyst 1.5 data system. Solvent composition will comprise tetrahydrofuran-methanol-water with 10 mM ammonium format, at the following ratios; solvent A 20:20:60 and solvent B 75:20:5. All lipid species will be separated under gradient conditions at 300 μL/min, the gradient starting at 0% solvent B to 45% solvent B over the first minute, to 55% solvent B over 6 min, up to 80% solvent B over 1 min, up to 100% solvent B over 2 min, holding at 100% solvent B for 2 min, quickly back to 0% solvent B over 0.2 min and then holding at 0% solvent B until the next injection at 15.5 min. A total of 338 lipid species will be analyzed by multiple reaction monitoring experiments. This type of lipidomic measure is semi-quantitative, because stable isotope internal standards are not available for each individual lipid species. However, the precision of such measures is considered good (average coefficient of variation (CV) typically < 10%). We will report fasting lipid concentrations to provide an indication of the relative abundance of each lipid species or class. Lipid concentrations reported for lipid classes and subclasses will be calculated from the sum of the individual lipid species within each class. Finally, the percentage change in lipid species (PRE to POST) will be compared between groups (control and intervention groups).

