#### Mechanistic analyses

##### Skeletal muscle biopsy

Percutaneous muscle biopsies will be performed in a random sub-sample of 20 patients at PRE and POST, immediately after the oral glucose tolerance test. In brief, muscle biopsies will be obtained under local anesthesia (2–3 mL of 1% xylocaine) from the muscle vastus lateralis, using a 5-mm Allendale needle with suction. Immediately after the biopsy procedure, the sample will be blotted dry and trimmed of visible adipose and connective tissue using a standard dissecting microscope. Four portions of the specimen (~ 30–100 mg) will be snap frozen in liquid nitrogen and stored at − 80 °C.

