##### Non-targeted analysis

We will perform RNA sequencing (RNA-seq; Fig. 5). Total RNA will be extracted, homogenized from ~ 20 mg of muscle tissue using TRIzol reagent (Invitrogen®), and isolated according to the RNeasy Fibrous Tissue Mini Kit (Qiagen®) protocol, using a Kinematica™ Polytron™ PT 1300 (FisherScientific®). Total RNA will be determined spectrophotometrically at 260 nm (GE Healthcare®) and RNA integrity number (RIN) will be checked by capillary electrophoresis using a Bionalyzer 2100 (Agilent®). For each sample, ~ 3 ul of total RNA extract will be delivered to the Pennington Biomedical Research Center Genomics Core for RNA sequencing (RNA-seq) analysis. Sample concentration will be normalized and complementary DNA (cDNA) pools will be created for each sample, and subsequently tagged with a barcoded oligo adapter to allow for sample-specific resolution. Sequencing will be carried out using an Illumina HiSeq 2500 platform (Illumina®) with a 50-bp single end reads. The quality of RNA-seq data will be checked using FastQC v0.10.0 (Barbraham Bioinformatics®). Alignment to the reference genome (rn5, UCSC), differential expression based on counts per million mapped reads (CPM), and post-analysis diagnostics will be carried out. RNA-seq data will be deposited in National Institutes of Health Gene Expression Omnibus (NIH GEO) and normalized CPM values for all measured genes will also be provided. To validate the RNA-seq data, gene and protein expression will be then determined by quantitative real-time PCR (qRT-PCR) and western blotting, as described in the following sections.

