##### Targeted analyses

Gene expression will be determined by qRT-PCR (Fig. 5). In brief, total RNA isolation, quantification, and purity will be carried out as described above. Gene expression will be determined by qRT-PCR analyses using the microglobulin (*B2M*) gene as a housekeeping gene. All qRT-PCR reaction mixtures will be prepared using a Superscript Platinum One-Step kit (Invitrogen, CA, USA) with incorporated Maxima SYBR Green/ROX qPCR Master Mix (Applied Biosystems, CA, USA) on a Step One Thermocycler (Applied Biosystems, CA, USA). The messenger RNA (mRNA) levels of the genes lipoprotein lipase (*LPL*), pyruvate dehydrogenase kinase 4 (*PDK4*), and aetyl-CoA carboxylase alpha (*ACACA*) will be analyzed. Potential genes that emerge from the RNA-seq analysis will be validated using qRT-PCR analysis. Relative change in gene expression (Δ-ΔCq) will be calculated by subtraction of the ΔCq at PRE (used as a calibrator) to the corresponding ΔCq at POST. Finally, fold change will be determined as 2-Δ-ΔCq. All sense and reverse primers used for each gene will be reported along with the results.

Protein expression will be determined by western blot (Fig. 5). In brief, muscle samples will be homogenized in ice-cold lysis buffer. Equal loading of samples (25–40 μg) and transfer efficiency will be monitored with the use of 0.5% Ponceau S staining of the blot membrane. Primary antibodies involved in the insulin signaling pathway (phosphorylated insulin receptor substrate 1 (pIRS-1 Ser 307), phosphorylated protein kinase B (pAkt Ser 473), Akt substrate of 160 kDa (pAS160), phosphorylated 5′ adenosine monophosphate-activated protein kinase (pAMPK Thr 172), and total glucose transporter type 4 (GLUT4)) and oxidative capacity (mitochondrial complexes (OXPHOS)) will be incubated overnight at 4 °C. For each protein, binding of the primary antibody will be detected by peroxidase-conjugated secondary anti-rabbit or anti-mouse antibodies using chemiluminescence detected by ImageQuant LAS 4000 (GE Healthcare®), quantified by densitometry (Scion Image®), and normalized to respective total protein or housekeeping proteins. Potential candidates emerging from RNA-seq analysis will be validated using western blot analysis.

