### Statistical analysis

Data normality will be tested using the Kolmogorov-Smirnov or the Shapiro-Wilk *W* test. Parametric data will be presented as mean ± 95% CI. Non-parametric data will be log-transformed and presented as back-transformed mean ± 95% CI. The ES (Cohen’s *d*) will be calculated and interpreted as small (0.2–0.4), medium (0.5–0.7), or large (≥ 0.8).

Generalized linear mixed model analyses will be performed for each dependent variable, with group and time as fixed factors and patients as a random factor; the models will be adjusted by age, BMI, disease activity, and if different between groups, baseline values of the outcome variable. In the case of significant *F* values, a post-hoc test with Tukey’s adjustment for multiple comparisons will be performed. Analyses will be conducted according to the intention-to-treat principle, in which missing values will be handled by the generalized linear mixed model by using maximum likelihood to estimate the parameters of the model. To test the influence of reducing sedentary time on health-related outcomes, patients will be allocated into “responder” and “non-responder” sub-groups (according to changes in sedentary time); thereafter, the dependent variables will be compared between them.

Data analysis will be performed using the SAS 9.3 (SAS Institute Inc., Cary, NC, USA) for Windows. The level of significance will be set at *p* ≤ 0.050.

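### Lipid comparison by per-patient percentage change can use only complete PRE/POST pairs and does not fit the mixed model the protocol prescribes for each dependent variable

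*Protocol article*

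**What the plan says.** **Lipidomics (non-targeted).** The samples: "PRE and POST intervention serum samples (10 μL) will be collected from a random sub-sample of 20 patients". Concentrations are reported descriptively: "We will report fasting lipid concentrations to provide an indication of the relative abundance of each lipid species or class". The only between-group comparison stated for lipids is that "the percentage change in lipid species (PRE to POST) will be compared between groups".

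**Statistical analysis.** A generalized linear mixed model is planned for each dependent variable, with group and time as fixed factors and patient as a random factor. Analysis is by intention to treat, and "missing values will be handled by the generalized linear mixed model by using maximum likelihood". Data that are not normally distributed are to be log-transformed and back-transformed for presentation.

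**Targeted analyses.** For qRT-PCR, the relative change in expression is obtained "by subtraction of the ΔCq at PRE (used as a calibrator) to the corresponding ΔCq at POST", and is then turned into a fold change. No between-group test is written there. The muscle comes from a sub-sample of the same size: "Percutaneous muscle biopsies will be performed in a random sub-sample of 20 patients at PRE and POST".

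**Non-targeted analysis.** RNA-seq uses differential expression on counts per million, not a per-patient change.

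**Sample size.** Dropout is put at about 25%.

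**The concern.** The lipidomics section and the general analysis section imply different treatment of a patient who gives a PRE sample and then withdraws. Under the mixed model her PRE value enters the likelihood. Under the percentage-change comparison she has no value to enter. The percentage change also has no time dimension, so it cannot be the dependent variable of a model with time as a factor. Two analysts working from this text could analyse different patients with different models.

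Two statistical weaknesses follow from the choice of measure. First, percentage change is right-skewed, and its mean is above zero even when nothing has changed. Second, a comparison of change among completers carries regression to the mean into the between-arm difference if withdrawal depends on the PRE level differently in the two arms. At stake is a clean reading of the lipid results, a mechanistic part of the trial that rests on 20 patients.

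**Working it through.** **Inputs from the protocol article.** Sub-sample of 20; dropout about 25%; two sampling times, PRE and POST. The recruitment figure that uses this dropout reproduces as 24 × 1.25 = 30 (dividing by 0.75 instead gives 32; nothing here turns on that).

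**Inputs assumed, because the protocol does not give them.** Ten sub-sample patients per arm; log-scale SD 0.3 to 0.5; PRE/POST correlation as stated at each step; the pattern of dropout.

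**1. Pairs available.** 20 × 0.75 = 15 patients with both samples. About 5 have PRE only.

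**2. Precision gained by keeping the PRE-only patients.** With completion share c = 0.75 and PRE/POST correlation ρ, the variance of the maximum-likelihood estimate of change, relative to the complete-pair change score, is [(1 + ρ) + (1 − ρ)c] / 2.

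| ρ | Ratio | Variance saved |
|---|---|---|
| 0.3 | (1.3 + 0.7 × 0.75)/2 = 0.9125 | 8.8% |
| 0.5 | (1.5 + 0.5 × 0.75)/2 = 0.9375 | 6.3% |
| 0.7 | (1.7 + 0.3 × 0.75)/2 = 0.9625 | 3.8% |
| 0.9 | (1.9 + 0.1 × 0.75)/2 = 0.9875 | 1.3% |

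The gain is small. For scale, the difference detectable with 80% power at two-sided 5% is 1.32 SD with 10 v 10 patients and 1.57 SD with 8 v 7. Most of that loss comes from the absent POST samples, which no model restores.

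**3. Skewness without any dropout.** If log PRE and log POST have the same mean, SD s and correlation r, the mean percentage change is exp(s²(1 − r)) − 1.
- s = 0.3, r = 0.7: exp(0.027) − 1 ≈ 3%.
- s = 0.5, r = 0.5: exp(0.125) − 1 ≈ 13%.

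This offset cancels between arms only if their baseline distributions match.

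**4. Bias when withdrawal depends on PRE in one arm.** Simulation with no true effect, 10 patients per arm and 3 lost per arm: at random in control, and with weight exp(1.5 × standardised PRE) in the intervention arm. There were 6000 runs per setting, and the exercise was done twice. It leaves 14 pairs, slightly fewer than the 15 of step 1. Bias in the between-arm difference of mean percentage change, in percentage points (first run / repeat):

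| Log SD | r = 0.5 | r = 0.6 | r = 0.7 |
|---|---|---|---|
| 0.3 | 5.4 / 5.0 | 4.5 / 4.3 | 2.9 / 3.3 |
| 0.4 | 6.6 / 7.0 | 5.2 / 5.7 | 4.5 / 4.1 |
| 0.5 | 8.5 / 10.0 | 7.9 / 7.4 | 5.0 / 5.7 |

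A log-scale estimate that conditions on PRE stayed within 0.01 log units of zero.

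**5. That bias against its noise.** The standard error of the between-arm difference was about 13 to 33 points (21 at SD 0.4, r 0.6). The bias is therefore about 0.2 to 0.3 of a standard error. A nominal 5% t test rejected in 4.9 to 5.9% of runs, against 4.0 to 5.2% when dropout was random. With dropout unrelated to PRE the bias was within ±0.5 points.

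**6. A second dropout model.** Here the log-odds of withdrawal rise by 1 per SD of PRE in the intervention arm only, giving about 25% v 28% dropout. The log-scale change score was off by 0.12 SD at ρ = 0.5 and 0.04 SD at ρ = 0.8. Maximum likelihood was off by about zero in both.

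**The case against.** The strongest reply is that no sentence excludes patients without a POST sample. The Statistical analysis section covers each dependent variable and allows log-transformation with back-transformation. A group-by-time contrast on log concentration, back-transformed, is itself a between-group comparison of relative change. On that reading the lipidomics section names the contrast and the general section names the model. This is a fair reading, and it shows that the remedy is already within the plan. It does not remove the point: the lipidomics section does not say so, and what it writes is a comparison of percentage changes.

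It can also be said that modelling detail for omics sub-studies is commonly left to a fuller document. That would answer an omission. Here the article states two approaches that do not fit together.

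Other parts of the reply stand:
- A reader might infer that all gene-expression results share the problem. They do not. RNA-seq is analysed on counts per million, and the qRT-PCR text only defines how a value is expressed. ΔΔCq is a log-scale difference, so the skewness criticism does not reach it either.
- A reader might infer that spurious lipid effects are likely. Nothing in the protocol suggests that withdrawal depends on baseline lipids, still less in one arm only. Even under that assumption, false positives stay near 5 to 6%.
- Retaining PRE-only patients adds little precision.

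**Conclusion.** The point holds as an inconsistency with a modest consequence. Read literally, the lipid comparison can use only about 15 of 20 patients at the protocol's own dropout, and it does not fit the intention-to-treat mixed model promised for each dependent variable. Percentage change is also a skewed measure, for which the planned model on the log scale is a better substitute.

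The size is small. The bias is a few percentage points, well below one standard error, and arises only if withdrawal depends on the PRE level differently by arm. The SDs, correlations, equal arms and dropout pattern behind these figures are all assumptions.

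It would go too far to say that the protocol drops withdrawals by rule or abandons intention to treat. Exclusion is implied by the arithmetic of the measure and is stated nowhere. For the qRT-PCR genes the point is only a precaution, should a between-group test be done on the fold change. The primary outcome, sedentary time, is not touched.

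**What to change.** **Lipidomics (non-targeted).** State that log lipid concentration at PRE and POST enters the mixed model of the Statistical analysis section for all sub-sample patients with a PRE sample. State that the between-arm effect is the ratio of geometric means (POST relative to PRE, intervention against control) from the group-by-time contrast. Keep individual percentage change as a descriptive display, with the number of pairs per arm.

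**Targeted analyses, qRT-PCR only.** State that any between-group test models ΔCq at PRE and POST in the same way, and that the resulting ΔΔCq contrast is back-transformed to a fold change for display.

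If a complete-pair analysis is really wanted, the alternative is to say so and to place it outside the intention-to-treat statement. That settles the inconsistency but leaves the skewness and the possible bias.

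**Cost.** About two sentences, with no new data and no new model. The small downside is that effects are reported as ratios and not as simple percentage changes.

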#### Assessment of anti-viral T cell function

We will assess anti-viral T cell function as a measure of overall immune competency using Enzyme linked immunospot (ELISpot) technology in a random sub-sample of 20 patients (Fig. 5). For this analysis, an additional blood sample (25 ml) will be drawn into sodium heparin vacutainers. Blood will be diluted 1:1 with Roswell Park Memorial Institute (RPMI) medium, and layered on top of lymphocyte separation medium for isolation of peripheral blood mononuclear cells by density gradient centrifugation using standard methods. Peripheral blood mononuclear cells will be frozen slowly (− 1 °C per minute in a Nalgene [name] freezing container) at − 80 °C, and after 12 h, stored in liquid nitrogen until assay. For the ELISpot assay, cells will be thawed rapidly to 37 °C, washed twice in RPMI (10% fetal calf serum, 1% penicillin and streptomycin) and rested for approximately 16 h in a humidified incubator (37 °C, 5% CO_2_). Cells will then be washed, counted, and added to polyvinylidene fluoride (PVDF) membrane plates (coated with anti-human IFN-γ antibodies) and stimulated for 16 h in separate conditions using immuno-dominant and conserved antigens from common viruses, including influenza, varicella zoster virus, Epstein Barr virus and cytomegalovirus. Stimulation will be via a human leukocyte antigen (HLA)-independent approach with overlapping peptides spanning the length of each antigen. Following stimulation, the ELISpot assay will be developed according to manufacturer instructions. These procedures will be undertaken in batches at the University of Sao Paulo, and stabilized assay plates will be shipped to the University of Bath in the UK for reading via an automated ELISpot plate reader (Autoimmun Diagnostika GmbH, Germany).

